### Program Content and Design

#### Text Messages

Essential Coaching for Every Mother consists of 53 standardized text messages that provide evidence-based information related to caring for a newborn and maternal mental health that all new mothers should know. Messages will be sent to participants from birth to 6 weeks postpartum, with 2 messages per day in the first 2 weeks and a daily message in weeks 3 through 6. The following topics are covered in the messages: postpartum anxiety, postpartum depression, maternal self-care, postnatal follow-up, breastfeeding or formula feeding, feeding, infant concerns, cord care, well-baby care, normal development, crying, and safe sleep. Women who receive the messages will be able to self-select breastfeeding or formula feeding messages. The TextIt platform will be used to program and schedule the messages [30], and Twilio will be used as the gateway service that offers virtual phone numbers and short codes that send and receive messages on behalf of the TextIt account [31].

#### Intervention Group

Participants in the intervention group will receive the standard in-person care in the hospital in which they give birth. After enrollment into the study, participants will start receiving messages until 6 weeks postpartum. The messages will be sent automatically based on the age of the infant. Participants in the intervention group will receive Essential Coaching for Every Mother as early as the evening of the second day after giving birth. This could be as early as 17 hours after birth (if a woman delivered at 11:59 the night before) or as late as 41 hours (if a woman delivered at midnight). If a participant enrolls after the messages are designed to start, they will start the message flow based on when they gave birth. Messages are sent at 10 AM and 5 PM during the first 2 weeks and at 10 AM daily after that. This time was recommended by both women and health care providers during the development of the intervention [23].

#### Control Group

Participants in the control group will receive the standard in-person care in the hospital in which they give birth. Women in the control group will not receive any study text messages but are not limited in their ability to seek additional postpartum support outside of the study. Data will be collected for both groups regarding postpartum support sought.

### Study Measures

The same data will be collected from all participants, regardless of their group allocation, via self-reported online surveys through Research Electronic Data Capture (REDCap) hosted at IWK Health. Upon enrollment and at 6 weeks and 6 months postpartum, all participants will be sent a text message with a link to a REDCap survey. Background demographics will be collected at baseline on outcomes such as maternal age, occupation, marital status, and education level. At 6 weeks, a follow-up survey will be conducted to collect data on whether mothers had any postnatal contacts for themselves or for their infant, health concerns, health information seeking, infant outcomes, the birth journey (including any intensive care stays), and infant feeding behavior. At 6 months, information on postnatal care and infant feeding behavior will be collected. Implementation data will be collected throughout the trial, and evaluation feedback will be collected at 6 weeks from women who received the intervention. Table 1 provides details of the data collected at each of the outcome assessment time points, and Figure 1 outlines the CONSORT flow diagram.

**Table 1 table1:** Data collected at the study outcome assessment time points.

Data collected			Enrollment		Baseline (T1)		6-week follow-up (T2)		6-month follow-up (T3)
**Enrollment**									
	Eligibility screen	✓							
	Informed consent			✓		✓		✓	
	Randomization	✓							
**Assessments**									
	Demographics			✓					
	Self-efficacy			✓		✓		✓	
	Social support			✓		✓		✓	
	Postpartum anxiety			✓		✓		✓	
	Postpartum depression			✓		✓		✓	
	Postpartum care and adjustment					✓		✓	
	Delivery experience					✓			
	Feeding experience					✓		✓	
	Health information seeking					✓			
**Implementation**									
	Quality					✓			
	Extent	✓		✓		✓			

**Figure 1 figure1:**
[figure not shown]
CONSORT (Consolidated Standards of Reporting Trials) flow diagram.

### Effectiveness Outcomes

The primary outcome of self-efficacy will be measured using the Karitane Parenting Confidence Scale (KPCS) [32]. This 15-item scale assesses the perceived self-efficacy of mothers of infants up to 12 months of age and has acceptable internal consistency (Cronbach α=.81) and test-retest reliability (*r*=0.88) [32]. A cutoff score of ≤39 (out of a possible 45) was determined to indicate a clinically low level of perceived parenting self-efficacy [32]. Additionally, a reliable change index of ≥6 was considered a significant change in their level of parental self-efficacy. Therefore, parents can be considered to have a high level of parenting self-efficacy if they either have a score above 39 or improve their score by 6 points, while still less than 39 [32]. This measurement will be collected at baseline and 6 weeks and 6 months postpartum.

Social support will be measured using the Multidimensional Scale of Perceived Social Support (MSPSS) [33]. This scale provides a measurement of how much support a parent feels they receive from family, friends, and a significant other, and 3 subscale scores (with 4 items per subscale) can be calculated as well as a total score (from 12 to 84), with total scores indicating greater perceived support. If the total score and subscale scores are averaged over items, scores between 1 and 2.9 are considered “low support,” 3 to 4.9 are considered “moderate support,” and 5 to 7 are considered “high support” [34]. The MSPSS has been shown to be valid and internally reliable, with Cronbach α values ranging from .81 to .94 on individual subscales and from .83 to .92 for the total score [33].

Postpartum anxiety will be measured using the Postpartum Specific Anxiety Scale (PSAS) [35]. The PSAS is a valid and reliable instrument for assessing anxiety during the first 6 months postpartum, with Cronbach α values for individual factors ranging from .80 to .91, with an overall α value of .95 [35]. The optimal cutoff PSAS score for detecting clinical levels of anxiety is 112, with a sensitivity and specificity of 0.75 [35].

Postpartum depression will be measured using the 10-item Edinburgh Postnatal Depression Scale (EPDS) [36]. This scale can be used to screen mothers at risk for developing postpartum depression, with a score above 14 (out of 30) indicating a likelihood of having or developing postpartum depression [36]. The sensitivity of the EPDS was found to be 86% in women with depressive symptoms and 78% in women without depressive symptoms [36].

### Implementation Outcomes

To measure the implementation extent of the Essential Coaching for Every Mother program, output data available through the Twilio and TextIt platforms [30,31] will be collected per participant including, but not limited to, enrollment rate, enrollment timing (postpartum or antenatal, days postpartum), number of withdrawals, and numbers of messages received. This data collection will continue throughout the trial and will be completed after the last follow-up contacts. To measure implementation quality, in the 6-week survey women in the intervention group will be asked about user experience, perspectives on the frequency and timing of messages, and what they liked and did not like about Essential Coaching for Every Mother. Using these measures, we seek to obtain data not only on implementation extent but also on the quality of the program through open-ended questions where mothers will be asked about their experience with Essential Coaching for Every Mother in practice.

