### Implementation Objective

The implementation objective is to evaluate the implementation extent (ie, enrollment rate and timing, withdrawal rate, number of messages received) and quality (ie, satisfaction, barriers, suggestions for improvement) of the Essential Coaching for Every Mother program.

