### Screening and Baseline

Interested participants will contact the research team via text message to complete the automatic remote eligibility screening process. All participants will receive a welcome message as well as details about the study and what the study will entail. During the antenatal recruitment process, the woman’s phone number, first name, and due date will be collected via TextIt [30]. This information is required to ensure that follow-up messages are sent to the woman via her mobile device based on her due date.

During the antenatal screening process, participants will be screened for eligibility, and eligible participants will be informed of the need to send a text within 10 days after giving birth to be enrolled in the study. Women who have not yet given birth are sent messages at 39 weeks, 40 weeks, 41 weeks, and 42 weeks or until enrolled or withdrawn to remind them of the need to text the word “delivered” after giving birth. Participants who initiate contact before 37 weeks will be asked if they want to be sent follow-up messages once they reach 37 weeks until the sample size is reached.

Once a woman gives birth or enrolls after giving birth, she will be asked screening questions to ensure eligibility and determine parity for stratification. Additional details including the newborn’s name, preferred gender pronoun for the infant, infant’s date of birth, and parity will be collected at that time. Once stratified, participants will be randomized and informed of their group allocation. Participants who are randomized to the intervention group will be asked their preference on breastfeeding and formula feeding messages. All participants will be asked to complete the consent form and baseline survey. To remind participants to complete the survey, reminder text messages will be sent via TextIt every other day for 2 weeks (a maximum of 6 total messages) or until the survey is completed. An email will be sent as a final reminder to participants who have not yet completed the survey after day 14. If an email address was not provided, an expanded text message will be sent on day 14 instead. Participants will also be informed that they may message “STOP” to withdraw from the study at any time. If a participant withdraws from the study, they will not receive any further messages nor will they be asked to complete any future surveys. Participants who complete the baseline survey will receive an electronic gift card worth Can $15 (US $11.97).

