### Follow-Up Assessments

At both 6 weeks and 6 months postpartum, all participants in both groups will be sent a text message asking them to complete a follow-up survey. Participants will be asked to provide consent, and once consent is given, they will start the survey. Participants who complete the follow-up surveys will receive an electronic gift card worth Can $15 (US $11.97) for each survey. To remind participants to complete the survey, reminder text messages will be sent via TextIt every other day for 2 weeks (a maximum of 6 total messages) or until the survey is completed. An email will be sent as a final reminder to participants who have not yet completed the survey after day 14. If an email address was not provided, an expanded text message will be sent on day 14 instead.

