For implementation data, summative data provided by the TextIt platform and Twilio interface will be reported, and descriptive statistics will be used to describe participants’ experiences with Essential Coaching for Every Mother using means and standard deviations or percentages, as applicable. Open-ended questions from the survey will be analyzed using thematic analysis [37]. Greater understanding of the implementation extent indicators, in combination with the qualitative responses from mothers, will offer insight into the “black box” of the intervention to explore reasons for success or failure [38].

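### Programme quality is asked only in the 6-week survey, and the single STOP route ends both messages and surveys, so women who stop the messages early give no quality data

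*Protocol article*

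**What the plan says.** The Implementation Objective has two halves. One is extent, which includes the withdrawal rate and the number of messages received. The other is "quality (ie, satisfaction, barriers, suggestions for improvement".

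Quality is measured once. Implementation Outcomes says that "in the 6-week survey women in the intervention group will be asked about user experience, perspectives on the frequency and timing of messages", together with likes and dislikes. Study Measures agrees: "evaluation feedback will be collected at 6 weeks from women who received the intervention". Table 1 marks Quality at the 6-week follow-up only.

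Follow-Up Assessments gives the general rule that "all participants in both groups will be sent a text message asking them to complete a follow-up survey". Screening and Baseline gives the exception. Participants may text STOP "to withdraw from the study at any time", and after that "they will not receive any further messages nor will they be asked to complete any future surveys". The article describes no other way out.

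Data Analysis uses different language for what appears to be the same event: it refers to women who asked for the messages to end, and lists them apart from those lost to follow-up. It also says that extent and quality together will be used to "explore reasons for success or failure".

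**The concern.** The messages run until 6 weeks and the quality items come at 6 weeks. Any woman who stops the messages by texting STOP does so before the quality questions are asked, and the withdrawal rule then keeps them from her. This is a stated rule, not a silence that a fuller document might fill.

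A hybrid effectiveness-implementation trial is meant to show what helps and what hinders real-world use. Women who leave part-way are an obvious source on barriers. As written, satisfaction and barrier results will describe women who stayed and answered, and the trial will know that others left without knowing why. The withdrawal count cannot fill the gap: the only exit offered is from the study, it is open to controls who receive no programme messages, and antenatal registrants can also be withdrawn before randomisation.

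**Working it through.** **Setting the sections side by side**

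1. Quality items: intervention arm, 6-week survey only (Implementation Outcomes, Study Measures, Table 1).
2. Who is sent that survey: all participants (Follow-Up Assessments), except those who have withdrawn (Screening and Baseline).
3. How a woman leaves: STOP, which is withdrawal from the study and ends messages and surveys together (Screening and Baseline).
4. From 1 to 3: a STOP before 6 weeks means no quality data from that woman.
5. What remains for her: the fact of withdrawal and the messages received, per participant, from the TextIt and Twilio platforms (Implementation Outcomes). The article describes no item that records her reason.
6. Data Analysis speaks of ending the messages where Screening and Baseline speaks of leaving the study, so programme exit and study exit are not told apart.

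**How far the satisfaction figure could move**

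The plan gives no satisfaction figure and no STOP rate. The nearest inputs are in Sample Size: 60 per group × 1.15 = 69, rounded up to 70, which reproduces the stated number; and 15.5% non-completion in the feasibility study, which covers all causes and not STOP alone.

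Let n = 70, r = women who answer, m = n − r, and s = proportion satisfied among those who answer. If nothing is assumed about the others, satisfaction among all n lies between s·r/n and (s·r + m)/n.

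- At 15.5%: 70 × 0.155 = 10.85, so m = 11 and r = 59. With s assumed at 0.90, the lower bound is 53.1/70 = 75.9% and the upper bound is (53.1 + 11)/70 = 91.6%.
- Assumed loss of 5% (m = 4, r = 66): 84.9% to 90.6%.
- Assumed loss of 10% (m = 7, r = 63): 81% to 91%.
- Assumed loss of 20% (m = 14, r = 56): 72% to 92%.

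**Direction**

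If a share d stops, and satisfaction is s among women who answer and t among those who stop, the reported figure exceeds the overall one by d × (s − t). It is too high whenever women who stop are less satisfied. With s = 0.90 and t = 0.30, both assumed:

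- d = 10%: 0.9 × 0.90 + 0.1 × 0.30 = 84%, so 90% is 6 points too high.
- d = 20%: 0.8 × 0.90 + 0.2 × 0.30 = 78%, so 90% is 12 points too high.

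**Why dividing by all randomised women is not a correction**

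Putting the satisfied women who answered over all randomised intervention women scores every missing woman as dissatisfied. Under the same assumptions this gives 0.9 × 0.90 = 81% against 84%, and 0.8 × 0.90 = 72% against 78%. It errs by 3 and 6 points the other way.

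**The case against.** The strongest reply is that the gap is small and partly covered. Extent data count each woman who stops and her messages. Women who dislike the messages but do not text STOP are still sent the survey, with up to six reminders and a final email or text, and are asked what they did not like. The analysis of quality is descriptive and thematic, no satisfaction threshold drives a decision, and the primary effectiveness result does not depend on it. Leaving withdrawn postpartum women alone is a defensible choice, and sending surveys to women who have left the study would break the rule stated to them. How withdrawals are tabulated may be settled in a fuller document.

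Much of this stands. It rules out several stronger conclusions that a reader might infer:

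- That the implementation objective leaves these women out altogether. It does not: extent includes them, and the gap is in quality.
- That the withdrawal count adds together two defined kinds of exit. Only one kind is defined, so the accurate statement is that the plan does not distinguish them.
- That women who stop are the women for whom the programme failed. The document gives no reasons for withdrawal, and some women who stay may be dissatisfied.
- That Table 1 is materially wrong because Extent is not marked at 6 months, although Implementation Outcomes continues collection until after the last follow-up contacts. This is a clerical mismatch that changes no result.

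The reply does not answer the central point. A stated rule excludes women who stop early from the only quality measurement, while the plan sets out to learn about barriers and reasons for failure.

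**Conclusion.** The point holds for the quality half of the implementation objective. Intervention women who text STOP before 6 weeks give no data on satisfaction, barriers or dislikes, and the plan does not separate leaving the programme from leaving the study.

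Reported satisfaction is likely to be overstated. That direction rests on the assumption that women who stop are less satisfied than those who answer, which is plausible but not shown in the document. The size cannot be estimated from it. A reader might take the 6 to 12 points above as an estimate, but the 90%, the 30% and the stopping rates are all assumed. The range of 75.9% to 91.6% also rests on an assumed 90%, and it borrows an all-cause non-completion rate. If few women stop, the effect is small. The effectiveness comparison is not affected by this point. It is a cheap improvement worth making.

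**What to change.** - Reconcile Screening and Baseline, Implementation Outcomes and Data Analysis on what stopping means. Let intervention women stop the messages while staying in follow-up, with the 6-week survey still sent unless they withdraw from the study. Women who withdraw from the study keep the present assurance of no further contact.
- Put one optional automated question on the reason for stopping in the STOP confirmation.
- Report message stops in the intervention arm separately from study withdrawals by arm.
- Beside the satisfaction figure, state how many women answered at 6 weeks out of all randomised intervention women. Do not count those who did not answer as dissatisfied.

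The cost is a small contact burden at exit and a minor amendment to the withdrawal wording in a trial that already has approval from two ethics boards and is recruiting. The message flow is already automated. Women who have already withdrawn under the current wording should not be contacted again, so their reasons stay unknown.

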### Data Analysis

Data will be analyzed on an intention-to-treat basis (excluding women who requested to stop receiving the messages or were lost to follow-up). Demographic characteristics on maternal age, marital status, education level, and delivery method will be expressed as means and standard deviations or percentages, as applicable, based on group allocation. Postnatal contacts for themselves and their infants, health concerns, and feeding behavior will also be expressed as means and standard deviations or percentages, as applicable, based on group allocation. Any significant differences in baseline characteristics, examined through a chi-square analysis or Mann-Whitney test, will be adjusted for in the analysis. A *P* value of 0.05 will be considered significant for all outcomes.

For the primary outcome of self-efficacy, a total score will be reported using means, standard deviations, and percentages. Analysis of covariance (ANCOVA) will be used to measure whether total self-efficacy scores differ between the 2 groups, with adjustments for the pretest scores and any significant baseline characteristics.

For the first secondary objective, an ANCOVA will be used to determine whether scores differ between the 2 groups on social support, postpartum anxiety, and postpartum depression, with adjustments for the pretest scores and any significant baseline characteristics. For the second secondary objective, a 2-way ANCOVA will be used to measure whether the mean difference of self-efficacy scores differs between the 4 groups (multiparous/primiparous and intervention/control), with adjustments for any significant covariates on self-efficacy, social support, postpartum anxiety, and postpartum depression. For the third secondary objective, a 2-way repeated-measures ANCOVA will be used to explore whether changes in the key psychosocial outcome variables varied over time.

For implementation data, summative data provided by the TextIt platform and Twilio interface will be reported, and descriptive statistics will be used to describe participants’ experiences with Essential Coaching for Every Mother using means and standard deviations or percentages, as applicable. Open-ended questions from the survey will be analyzed using thematic analysis [37]. Greater understanding of the implementation extent indicators, in combination with the qualitative responses from mothers, will offer insight into the “black box” of the intervention to explore reasons for success or failure [38].

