### Inclusion Criteria

Participants will be recruited antenatally and postnatally. To enroll antenatally, participants must (1) be at least 37 weeks pregnant; (2) have daily access to a mobile phone with text messaging capabilities; (3) be ≥18 years of age; (4) live and give birth in Nova Scotia; and (5) speak and read English. To enroll postnatally, participants must (1) have an infant younger than 10 days of age; (2) have daily access to a mobile phone with text messaging capabilities; (3) be ≥18 years of age; (4) live and gave birth in Nova Scotia; and (5) speak and read English.

Participants will be excluded if (1) their newborn dies or is expected to die prior to leaving the hospital; (2) they have no access to a mobile phone, either personal or shared; (3) they are unwilling to receive text messages; (4) they decline to participate or withdraw; or (5) they previously participated in the development or feasibility phase of this project.

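### The analysis set labelled intention-to-treat excludes women for stopping the messages or being lost to follow-up, both after randomisation, so it is not intention-to-treat and can discard observed 6-week scores

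*Protocol article*

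**What the plan says.** The Data Analysis section of the protocol article states one analysis set. Data will be "analyzed on an intention-to-treat basis (excluding women who requested to stop receiving the messages or were lost to follow-up". The primary ANCOVA of total self-efficacy score (KPCS), adjusted for pretest score, comes under this statement, and no other set is named.

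Four other statements decide who is affected:

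- **Programme messages.** Under Text Messages, "Essential Coaching for Every Mother consists of 53 standardized text messages". Under Control Group, "Women in the control group will not receive any study text messages".
- **Opting out.** Under Screening and Baseline, "Participants will also be informed that they may message “STOP” to withdraw from the study at any time". The offer is not limited to one arm. After withdrawal, "they will not receive any further messages nor will they be asked to complete any future surveys".
- **Survey texts.** Under Follow-Up Assessments, "all participants in both groups will be sent a text message asking them to complete a follow-up survey", with up to six reminders per survey.
- **Timing.** Under Screening and Baseline, "Once stratified, participants will be randomized and informed of their group allocation". The Blinding section confirms that participants know their arm.

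**The concern.** An intention-to-treat analysis keeps each woman in the arm to which she was randomised, whatever she later does with the intervention. This rule removes women because of what they did after randomisation and with knowledge of their arm. Randomisation no longer guarantees that the sets compared are alike, yet the result would be reported as intention-to-treat.

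The two arms also differ in what there is to stop. One receives a stream of programme texts for six weeks and the other receives survey texts only. Requests to stop are therefore likely to be more common in the intervention arm, or to come from different kinds of women.

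The STOP procedure adds to the loss. It is the only opt-out described, and it closes data collection as well as the programme. A woman who merely wants no more texts loses her 6-week score.

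**Working it through.** **1. Is the set intention-to-treat?** Randomisation takes place after birth and before the messages and follow-up surveys. A request to stop and a loss to follow-up can only come later. Both exclusions are therefore post-randomisation, and the label does not fit the rule.

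**2. Which women leave the 6-week comparison?**

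- A woman who texts STOP before 6 weeks is not surveyed again. She has no 6-week score, so for her the rule amounts to a complete-case analysis.
- A woman who completes the 6-week survey and then texts STOP, or does not answer at 6 months, has a primary outcome on file. The exclusion has no time limit, so read literally she is removed as well. This is loss of observed data.

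**3. The plan's own figures.** The Sample Size section needs 60 per group and adds 15%: 60 × 1.15 = 69, rounded to 70, so 140 in total. This reproduces. The feasibility incompletion rate of 15.5% applied to 140 gives 0.155 × 140 = 21.7, about 22 women, or about 11 per arm if balanced.

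**4. Possible bias.** Let d1 and d0 be the shares excluded from the intervention and control arms. Let g1 and g0 be the mean score of retained women minus that of excluded women in each arm. Dropping the excluded women raises an arm's mean by d × g, so

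bias = d1 × g1 − d0 × g0.

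With 70 randomised per arm and SD 4.5,

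SE = 4.5 × √(1/[70(1 − d1)] + 1/[70(1 − d0)]).

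The two-sided type I error with no true effect is 1 − Φ(1.96 − bias/SE) + Φ(−1.96 − bias/SE).

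The SD of 4.5 and the reference effect of 3.78 come from the Sample Size section, where they describe pre-post change in the feasibility study. The exclusion rates by arm and the gaps (3 or 4.5 points, the latter one SD) are assumptions. A two-sided 5% test is also assumed, because sidedness is not stated. The table uses the same gap in both arms.

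| Excluded, intervention vs control | Gap | Bias (points) | SE | Type I error |
|---|---|---|---|---|
| 15.5% vs 15.5% | 3 or 4.5 | 0 | 0.83 | 5.0% |
| 15.5% vs 10% | 3 | 0.17 | 0.81 | 5.5% |
| 15.5% vs 10% | 4.5 | 0.25 | 0.81 | 6.1% |
| 15.5% vs 5% | 4.5 | 0.47 | 0.80 | 9.0% |
| 5% vs 0% | 3 | 0.15 | 0.77 | 5.4% |
| 15.5% vs 0% | 4.5 | 0.70 | 0.79 | 14.2% |

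Example: 15.5% vs 10% with a gap of 4.5 gives (0.155 − 0.10) × 4.5 = 0.25. The top value, 0.155 × 4.5 = 0.70, is about 18% of 3.78. If excluded women score higher than retained women, every bias changes sign.

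**The case against.** Several stronger readings are tempting, and the documents do not support them.

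- **That only the intervention arm can be excluded for stopping messages.** This is true of programme messages only. STOP is offered to participants generally, controls receive survey texts and reminders, and loss to follow-up applies to both arms. Unequal exclusion is likely, but exclusion from one arm alone is not what the article says.
- **That type I error rises to 14%.** That value needs no control exclusions and a full-SD gap. The 15.5% is overall incompletion in a single-group pre-post study, not a rate of stopping messages, and the plan inflates both groups alike. The ANCOVA also adjusts for pretest score, so only the gap left after that adjustment counts.
- **That the bias favours the programme.** Women who are struggling may stop, but so may confident women who do not need the texts. Nothing in the article settles this.
- **That the exclusion criteria also remove women after randomisation.** The entry "they decline to participate or withdraw" stands in the eligibility list, and the article elsewhere uses withdrawal for women followed antenatally, before randomisation. A pre-enrolment meaning is open.

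It can also be said that most early stoppers have no score, so relabelling alone recovers nothing for them. That is right. Imputation from baseline score and parity would not remove the bias either, if stoppers differ in ways those variables do not capture. Finally, a protocol article may leave the missing-data method to the analysis plan, so its absence is not held against this one.

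What survives is that the article does state the analysis set, states it in contradiction to its label, and by its wording can remove scores already collected.

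**Conclusion.** The point holds in this form. The only stated analysis set is called intention-to-treat and is not. It excludes women on post-randomisation behaviour in an unblinded trial, probably unevenly between arms. It can discard observed 6-week scores, and the STOP procedure loses others that could have been collected.

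The size and direction of bias cannot be known from the documents. Under the assumed gap of 3 to 4.5 points, bias is nil with equal exclusions and equal gaps and about 0.2 points with moderately unequal exclusions. It is about 0.7 points at the extreme of the range examined. The case for correction rests on the mislabelled set and the avoidable loss of data, not on any one of these figures.

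**What to change.** 1. Replace the analysis-set sentence with: *All randomised women are analysed in the arm assigned, whatever messages they received or stopped, and every available 6-week score is used.* Keep the present set only as a labelled sensitivity analysis. Because the article describes consent after randomisation and disclosure of the arm, say also how women who are randomised but never consent are counted.
2. For women still to be followed, separate a request to stop messages from a request to leave the study. Keep sending the 6-week and 6-month surveys to those who only stop messages.
3. For scores that remain missing, add a sensitivity analysis that lets stoppers differ from completers by a stated range. If this is not done, drop the intention-to-treat label and describe the analysis as complete-case.

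The planned 140 does not change. The cost is a wording change, one more branch in the TextIt flow and a minor ethics amendment. Recruitment was already open, so the new opt-out would cover only some participants, and women who have already withdrawn were promised no more surveys. The estimated effect may become smaller.
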